### Information collected via other sources:

#### **Nutritional assessments**

Both arms of the study will partake in nutritional assessments at baseline and the clinic endpoint (12 months). Evaluations will include assessment of dietary intake and dietary quality. Body weight and muscle strength will be measured. Body composition will be analysed.

**Dietary intake:** Dietary assessments will be conducted by a dietitian. This includes two 24 Hour Dietary Recalls and a Food Frequency Questionnaire (Appendix 3) at baseline and the clinic endpoint (12 months). Portion sizes will be validated through the use of a food atlas.

- **24 Hour Dietary Recall:** Following assessment of the 24h diet recalls, the clinic dietitian will assign appropriate food codes to each item reported. Data analysis will be limited to the McCance and Widdowson's composition of foods integrated dataset, the USDA Food Composition Databases and the Irish food composition databases. Food coding will be completed following each individual dietetic assessment. A food code data base will be generated and expanded upon following extraction of new food codes from each new 24hour diet recall recorded. This data will be analysed using Nutritics, web-based nutritional analysis software to capture diet intake assessing macro- and micronutrients, and specific food and nutrients directly relating to the dietary quality outlined in the WCRF framework for cancer prevention. All reference data will be assessed within-individual comparison and between-individual comparison. All data will be exported from Nutritics into a Microsoft excel file for processing with the study statistician.

- Food Frequency Questionnaire:** Individual and collective sample data captured from the EPIC-Norfolk Food Frequency Question (FFQ) will be entered in to the FFQ processing tool, FETA (Φετα) FFQ EPIC Tool for Analysis, which is based on the earlier CAFÉ system (Welch et al. 2005). The FETA tool is free to use and will produce different levels of nutrient data, as well as basic food groups and food patterns. This programme is based on version 6 (CAMB/PQ/6/1205) of the EPIC-Norfolk FFQ. FETA calculates the average daily intake of 46 nutrients and 14 food groups, for each individual. The default nutrients list provides a description of each nutrient/food group and the units used. The nutrient data for the FFQ foods have come from McCance and Widdowson's "The Composition of Foods (5th edition)" and its associated supplements. In FETA, the frequency category is converted into a portion multiplier (e.g. once a week =  $1/7 = 0.14$ ). After multiplication with the portion size, an average daily food weight for each of the 130 FFQ items is obtained. These weights are multiplied by the nutrient composition per gram to obtain the nutrient composition of the actual amount eaten. After summing all FFQ items for a participant, an average daily nutrient intake is obtained. Individuals with more than 10 missing lines of data will be excluded. The top and bottom 0.5% of the ratio of energy intake to estimated basal metabolic rate will be flagged as extreme outliers of nutrient intakes. All data will be exported from FETA data processing report into a readable Microsoft excel file for processing by the study statistician.

#### Information collected via the study database in the EDC:

**Data related to patient comorbidities, medication, and clinician record of actions/follow-up at survivorship and symptom management encounters:** Data relating to resource utilisation will be collected on an ongoing basis for the intervention group and at the end of the study for the control group. Data relating to survivorship services that were provided by the CUH and used during the 12 month period will be extracted from the patient records. Data on service utilisation (outside of CUH) will be collected at T0 and T12 by the information provided from the patient through the study patient's diaries (appendix 12); this will include the services used, frequency of use, duration of each service and the personnel responsible for providing the service. This information will be collected by the Research Nurse.

#### **Nutritional assessments:**

*Dietary quality* will be measured using the WCRF/AICR standardised scoring system which was discussed earlier. This also includes assessment of their alcohol intake, whether mothers' breastfed their babies and for how long.

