### 2.3. Secondary Objectives:

- To describe the symptoms experienced by patients with breast and gynaecologic cancers and evaluate the impact of the intervention on select reported symptoms over a 12-month period.
- To evaluate the impact of the survivorship clinic on quality of life using serial ePRO measures.
- To explore self-care agency and its relationship to quality of life and symptoms experienced in both arms.
- To evaluate adjuvant endocrine therapy medication adherence rates at 12 months after study entry in both arms, and factors associated with non-adherence in early-stage HR-positive breast cancer patients.
- To explore and assess the satisfaction of patient and Health Care Professionals with the intervention and to determine their perceptions of the systems usability.
- To estimate the resource use and economic impact of a women's malignancy survivorship clinic.
- To evaluate the impact of a dietetic intervention by assessing changes in dietary intake and diet quality over a 12-month period.
- To evaluate the impact of a dietetic intervention on body weight, lean body mass, fat mass, muscle strength and nutritional risk over a 12-month period.

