**C) Malnutrition Screening Tool:** The MST is a simple, quick, valid and reliable tool which can be used to identify patients at risk of malnutrition. It asks participants if they have lost weight recently without trying (and if so, how much) and if they have been eating poorly because of a decreased appetite (Ferguson et al. 1999). Patients identified at nutritional risk in the intervention arm only, will be advised on an appropriate nutrition care plan. Some patients may require ongoing monitoring, nutritional counselling and review of personal nutrition care plans. These patients will be invited to attend the ongoing dietitian clinic. The need for follow up review and number of sessions required for each patient will be decided by the clinic dietitian based on clinical judgment. In the case where the dietetic caseload may exceed the capacity of the survivorship clinic, an acceptance and

non-acceptance criteria for the dietetic clinic caseload was developed and will be used if required (Appendix 3b). These criteria will ensure that patients requiring more intensive and/or specialised dietetic support will be offered appropriate dietetic care in a timely manner.

**D) Physical activity:** a short validated physical activity questionnaire will be used (Danquah et al 2018) to measure physical activity levels. Physical activity is a fundamental Cancer Prevention Recommendation of the World Cancer Research Fund/American Institute for Cancer Research (WCRF/AICR) framework for cancer prevention. It will be measured as moderate to vigorous physical activity in minutes per week. It will be included in the (WCRF/AICR) standardised scoring system (Shams-White et al 2019). This is a practical tool that operationalises eight out of ten 2018 WCRF/AICR cancer prevention recommendations. The score enables researchers to assess the degree to which people adhere to the Cancer Prevention Recommendations and the health effects of doing so. The WCRF/AICR score is an accumulation of points assigned for adhering – or not adhering - to each of the components of the Cancer Prevention Recommendations or sub-recommendations. However, physical activity won't be included in the triggers.

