#### **Anthropometric measures:**

- Body weight:** Weight will be recorded with the participant wearing light clothes and no shoes on the same scale at the baseline clinic visit and at the clinic endpoint (12 months). Additionally, the intervention arm will also self-assess their weight

using the same personal scales at home, at the same time of the day, at baseline and at 2 monthly intervals until and including the endpoint of the study. Participants in the intervention arm will report their weight on the same day their weight has been recorded at home through their two monthly ePRO surveys.

- **Height:** The participant's height will also be measured at baseline in clinic.
- **Body Mass Index (BMI):** This will be calculated using the participant's weight and height and is part of the WCRF/AICR scoring system.
- **Body Composition:** Segmental body composition will be analysed using Bioelectrical Impedence Analysis (BIA) with the Body Composition Monitor (BCM) (Fresenius Medical Care, Bad Homburg, Germany). This is used for an accurate and objective assessment of overall body composition and hydration status (Baumgartner et al, 1988). The BCM device calculates the LBM, lean tissue index (LTI), fat tissue index (FTI), body cell mass (BCM), and adipose tissue mass (ATM), extracellular (ECW), intracellular (ICW) and total body water (TBW) based on measurement values, using physiological modelling and mixture equations (Cole-Cole plot and Hanai formulae and Chamney et al, 2007).
- **Waist circumference:** This measurement will be recorded with the participant not wearing clothing that is directly over the skin. If this is not possible, the measurement may be taken over light clothing. This is also part of the WCRF/AICR standardised scoring system.
- **Muscle strength:** Hand grip strength (HGS) will be measured using the Jamar dynamometer (Jamar Hydraulic Hand Dynamometer, Model 091011725, Sammons Preston Roylean, Nottinghamshire, UK) with its handle in the second position as recommended by the American Society of Hand Therapists (ASHT)(Fess,1986). Grip strength will be measured 3 times per hand, alternating between left and right hand to allow rest and account for any fatigue.
- **Nutritional risk:** Participant's nutritional status will be monitored over the 12 month period on the study database by assessing any change in their Body Composition and MST score.

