### **Nutrition for the intervention arm**

The nutrition intervention will include a personalised approach to nutrition education for patients in the intervention arm only. Patients will complete a symptom survey at 2 monthly intervals throughout the study. The symptom survey will act as screening tool to identify nutritional risk. Patient specific nutrition counselling will be offered to patients identified at risk.

***Diet Education and Personalised Nutrition Counselling:*** The main goal of the nutritional intervention is to improve the diet quality of each patient using a standardized nutrition assessment, offering evidence-based diet education and developing personalized nutrition goals. Individual goals and targets will be set during the 1st consultation. Dietary counselling involves the prescription of a therapeutic diet that uses regular foods, which can be further modified to provide for individual requirements. The therapeutic diet is adjusted to the individual's usual diet, thereby recognizing personal eating patterns and preferences, which form the basis for individualized dietary counselling. The prescription identifies the type, amount, and frequency of feeding and specifies the caloric/protein level to attain, together with any restrictions and limited or increased individual dietary components. In addition, nutritional advice can be adapted to respond to specific nutrition impact on symptoms (e.g. dysphagia, constipation, diarrhoea, altered taste and temperature sensitivity). Energy and protein requirements will be calculated only for patients that require specific caloric and protein targets to meet their individualised nutritional goals.

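### Diet quality is measured with a lifestyle score that also counts activity, BMI, waist and breastfeeding, so an arm difference in the total cannot be attributed to diet quality

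*Protocol*

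**What the plan says.** Section 2.3 lists this secondary objective: "To evaluate the impact of a dietetic intervention by assessing changes in dietary intake and diet quality over a 12-month period". A separate objective covers body weight, lean and fat mass, muscle strength and nutritional risk. Section 4.4.6, on nutrition for the intervention arm, states: "The main goal of the nutritional intervention is to improve the diet quality of each patient".

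Section 4.4.5 names the instrument. Dietary quality "will be measured using the WCRF/AICR standardised scoring system which was discussed earlier. This also includes assessment of their alcohol intake", and of whether mothers "breastfed their babies and for how long". Other parts of Section 4.4.5 add to the content of the score:

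- Physical activity: "It will be included in the (WCRF/AICR) standardised scoring system".
- BMI "is part of the WCRF/AICR scoring system".
- Waist circumference: "This is also part of the WCRF/AICR standardised scoring system".

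The physical activity paragraph also describes how the score is built. It covers eight of ten cancer prevention recommendations, and points for adherence to each component are added up. No weights are given and no diet-only sub-score is named.

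Both calendars (Sections 5.1 and 5.2) have a diet quality row with the WCRF/AICR score in brackets, at baseline and 12 months. The intervention calendar also has a second row for the WCRF/AICR score alone. The control calendar does not.

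**The concern.** The outcome and the construct do not match. On the protocol's own account the score measures adherence to a set of lifestyle recommendations, of which diet is only a part. A woman who becomes more active, or whose BMI or waist changes, gets a different score even if she eats exactly as before. Under the present text that would be reported as a change in diet quality.

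This could plausibly differ by arm. Only the intervention arm receives the symptom pathways, which include fatigue and joint pain, and the dietitian's education on lifestyle as well as diet. Activity or weight could therefore shift in that arm without better eating. Body weight and fat mass already have their own objective, so one change in body size could appear under two objectives, once labelled as diet quality.

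What is at stake is the reading of one secondary result and its use in planning a later trial. A difference in the total could be taken as evidence that the dietetic component improved diet when it did not.

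**Working it through.** The plan gives no SD, effect size or target for this outcome, and Section 4.2 makes no power calculation, so there is no stated figure to reproduce. The check is a trace of the score's content, followed by an illustration.

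**Content of the score, from Section 4.4.5**

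| Component named in the protocol | Dietary? | Can change in 12 months? |
|---|---|---|
| Food and nutrient items | yes | yes |
| Alcohol | not stated | yes |
| Physical activity | no | yes |
| BMI | no, though diet can affect it | yes |
| Waist circumference | no, though diet can affect it | yes |
| Breastfeeding history | no | essentially fixed |

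Because points are added, a change in activity, BMI or waist changes the total with the diet items held constant. This step needs no assumption about weights.

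**Illustration of size.** Assumptions, none of them in the protocol: eight equally weighted components; independent changes with equal SD, set to 1; breastfeeding fixed. Let k be the number of diet components, m the number of non-diet components that can change, and let each affected component shift by one unit.

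- Diet sub-score, standardised shift: k/√k = √k.
- Total, if only diet items shift: k/√(k+m), which is √(k/(k+m)) of the sub-score value.
- Total, if the b body-size components shift as much as each diet item: (k+b)/√(k+m).

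| Way of counting | Non-diet share | k, m, b | Ratio, diet items only | Total against sub-score, body size shifts too |
|---|---|---|---|---|
| BMI and waist as one | 3/8 = 37.5% | 5, 2, 1 | √(5/7) = 0.85 | 6/√7 = 2.27 against √5 = 2.24 |
| BMI and waist separate | 4/8 = 50% | 4, 3, 2 | √(4/7) = 0.76 | 6/√7 = 2.27 against √4 = 2.00 |
| Separate, alcohol not counted as diet | 5/8 = 62.5% | 3, 4, 2 | √(3/7) = 0.65 | 5/√7 = 1.89 against √3 = 1.73 |

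If the intervention moves only diet items, the total has 0.85 to 0.65 of the sub-score's standardised effect. If it moves body size equally, the dilution disappears. In the other direction, going from no credit to full credit for activity alone would move the total by 1/8 = 12.5% of the scale with no dietary change.

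**The case against.** The strongest reply is that diet is measured directly anyway. Both arms have two 24-hour recalls and a food frequency questionnaire at baseline and 12 months. Section 4.4.5 plans to analyse the recalls for foods and nutrients tied to dietary quality in the WCRF framework, and the questionnaire for 46 nutrients and 14 food groups. This stands. A reader might infer from the mismatch that the diet-quality objective cannot be answered; the documents do not support that. The objective covers dietary intake as well, and the score itself contains diet items.

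A second reply is that the protocol speaks of a scoring system with points per component, so a dietary sub-score may be intended and a SAP could define it. The extra row in the intervention calendar might even separate diet quality from the total. This stands only in part. The text and both calendars name the WCRF/AICR score as the diet-quality measure without restriction, so a SAP using a sub-score would be narrowing what the protocol fixes. The second row appears in one arm only, so it does not settle the question.

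A reader might also infer that past breastfeeding drives spurious change, or biases the arm comparison between women with and without children. Neither follows. The item is essentially constant over 12 months, so it drops out of change from baseline and adds only fixed variation between patients. Randomisation protects the arm contrast from systematic imbalance in parity. How the score treats women without children is not stated.

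Finally, the education delivered covers lifestyle as well as diet, so the total is a sensible outcome for the whole package. That is right, and is a reason to keep it under its own name. It is also true that a sub-score would not separate the dietitian's contribution from that of the nurse pathways, which are given in the same arm; that is a separate matter.

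**Conclusion.** The point holds as one of construct and label. As written, the protocol reports an additive lifestyle score as diet quality, and a between-arm difference in that total cannot be attributed to diet quality. This rests only on the protocol's own description of what the score contains and that its points are summed.

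Its numerical effect is not established. A reader might take a loss of about 15% in standardised effect (1 − 0.85) as the size. That figure depends on equal weights, on counting BMI and waist as one component, and on a dietetic intervention having no effect on weight. None of these is in the documents, and the last is doubtful.

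Severity is minor to moderate. The outcome belongs to one of eight secondary objectives in a feasibility trial with no efficacy sample size. It is, however, the stated main goal of the nutrition component, and the correction is cheap.

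**What to change.** - In Section 4.4.5 and in both calendars, define the diet-quality outcome as the dietary components of the WCRF/AICR score. List them, and state whether alcohol is included.
- Derive it from the recalls and food frequency questionnaire already taken in both arms at baseline and 12 months.
- Report the total separately, as adherence to the cancer prevention recommendations.
- Analyse BMI and waist under the body-weight and composition objective.
- Reconcile the stand-alone WCRF/AICR row in Section 5.1 with Section 5.2, so that both arms show the same outcomes.

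The cost is wording and one derived variable, with no new data. A small drawback is that a dietary sub-score is less directly comparable with publications that use the total; reporting both largely meets this.

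### Diet quality is measured with the whole WCRF/AICR adherence score, which also counts physical activity, BMI and waist, so it can change over 12 months with no change in diet

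*Protocol*

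**What the plan says.** One of the eight secondary objectives in Protocol section 2.3 reads: "To evaluate the impact of a dietetic intervention by assessing changes in dietary intake and diet quality over a 12-month period". The next objective covers body weight, body composition, muscle strength and nutritional risk separately. In section 4.4.6, under Nutrition for the intervention arm, the aim is put more strongly: "The main goal of the nutritional intervention is to improve the diet quality of each patient".

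The measure is fixed in section 4.4.5, where dietary quality "will be measured using the WCRF/AICR standardised scoring system which was discussed earlier". In both calendars (5.1 and 5.2) the diet quality row names the same score, at baseline and month 12.

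Section 4.4.5 also describes what the score contains:

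- **Purpose:** "The score enables researchers to assess the degree to which people adhere to the Cancer Prevention Recommendations".
- **Scope:** "This is a practical tool that operationalises eight out of ten 2018 WCRF/AICR cancer prevention recommendations".
- **Physical activity:** "It will be included in the (WCRF/AICR) standardised scoring system".
- **BMI:** calculated from weight and height "and is part of the WCRF/AICR scoring system". The waist circumference entry says the same of waist.
- **Alcohol and breastfeeding:** "This also includes assessment of their alcohol intake, whether mothers' breastfed their babies and for how long".

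**The concern.** The name of the outcome and its content do not match. Diet quality is about what a patient eats and drinks. The score assigned to it is a composite of diet, activity and body size. If the protocol is followed as written, a gain in activity or a fall in BMI or waist can be reported as better diet quality while the recalls and food frequency questionnaire show no change. The reverse can also happen: a rise in BMI or waist can cancel a real improvement in diet.

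There is also overlap between outcomes. Body weight has its own objective, yet BMI feeds the diet quality score, so one change in weight can appear under both.

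Section 6.0 says the between-group estimates are meant to inform a later efficacy trial. A mislabelled outcome would be carried into that design.

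**Working it through.** The protocol states no figure on this point, so there is none to reproduce. The check is to trace the outcome through the text.

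1. **Outcome.** Section 2.3: change in diet quality over 12 months, listed beside dietary intake and apart from body weight and composition.
2. **Instrument.** Section 4.4.5 and the diet quality rows of calendars 5.1 and 5.2: the WCRF/AICR score. None of these places names a diet-only part of it.
3. **Non-diet content that can change in 12 months.** Physical activity (4.4.5, item D), BMI and waist circumference (4.4.5, Anthropometric measures). All three are stated by the protocol to be in the score.
4. **Can it move without diet?** Item D describes the score as points added up across components. Suppose, for illustration, that a component is worth one point. A patient whose eating is unchanged but who moves from not meeting to meeting the activity recommendation changes by +1 on the total and by 0 on the food, drink and alcohol components. The total is what would be reported as diet quality.
5. **Can the arms differ this way?** Under Nutrition for the intervention arm, every patient in that arm is taught about lifestyle as well as diet, on the basis of the WCRF recommendations. A between-arm difference in activity or body size is therefore a plausible result of the intervention itself.

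**Rough size, on an assumption.** The protocol gives the number of recommendations scored (8) but neither the points per component nor a full list. Assuming equal points:

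- Activity plus body size, with BMI and waist as one component: 2/8 = 25%.
- Activity, BMI and waist counted separately: 3/8 = 37.5%.

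This is the share of the score that is not diet and can change within a year. It is not an estimate of bias, which would need the actual points and the actual changes.

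**The case against.** The strongest reply is that the protocol leaves room for the right reading. Under 24 Hour Dietary Recall it links dietary quality in the WCRF framework to particular foods and nutrients, and calendar 5.1 has one row for diet quality and another for the WCRF/AICR score. A diet sub-score is a derivation from data already held, which an analysis plan could define. This part stands: the text is ambiguous, and nothing says the total alone will be reported. It does not remove the point, because the sentence that names the measure, and the diet quality rows of both calendars, assign the score without restriction. The second row in 5.1 has no counterpart in 5.2, and the difference between the two rows is not explained.

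A second reply is that the score suits what the dietitian teaches, since the education covers lifestyle too. That makes the total a reasonable outcome of the education. It does not make it a measure of diet.

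Some stronger readings are tempting but not supported:

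- **Breastfeeding drives a difference between arms.** It is in the score, but the history is essentially fixed over 12 months and adds almost nothing to change.
- **Symptom pathways raise activity.** The protocol names pathways such as joint pain and fatigue but does not say they affect activity, and their appendices are not shown. Both arms may be given exercise and walking resources.
- **The extra components cost precision or sample size.** The protocol gives no weights or variances, and the trial was not sized on an effect (section 4.2).
- **Effects cannot be credited to dietetics because the whole clinic package is randomised.** That would apply equally to intake, weight and grip strength. It is a separate question that does not depend on the score.
- **Control patients lack the score.** The control diet quality row carries it at both time points.

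**Conclusion.** The point holds, as a minor one. As written, the protocol measures diet quality with a score that it says also counts activity, BMI and waist. The 12-month change can therefore differ between arms without a change in diet, and weight change is partly counted under two objectives. This conclusion rests on the protocol's own description of the score. Only the 25% to 37.5% share depends on the equal-points assumption.

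The consequence is limited. Diet quality belongs to one of eight secondary objectives in a feasibility trial. The primary endpoint, completion of the ePRO surveys (section 3.3), is unaffected. The separate intake data would also let a careful reader see when the score and the diet disagree.

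**What to change.** - In section 4.4.5, define diet quality as the sum of the food, drink and alcohol components of the WCRF/AICR score, derived from the recalls, the food frequency questionnaire and the alcohol assessment.
- Report the total score separately, named as adherence to the WCRF/AICR recommendations.
- Give calendars 5.1 and 5.2 the same two rows: diet quality sub-score and total score.

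The cost is one derived variable, one added row in the control calendar, and relabelling. No new data are collected and patients carry no extra burden, because both arms already have these assessments at baseline and month 12. The drawback is that a diet-only sub-score is less comparable with other studies than the standard total, which is why both should be reported.
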